#### Inclusion and Exclusion Criteria

Inclusion criteria are (1) age 60 and older and (2) ability to speak sufficient English or Spanish to complete assessments. These criteria are established to ensure that participants can fully engage with the study materials and accurately report their experiences. Individuals with dementia based on the AD8 or previous diagnosis of dementia, severe auditory or visual loss, and lack of access to either an internet connection or telephone will be excluded. The AD8 is an 8-item cognitive screening test sensitive to detecting early cognitive changes associated with common dementias including Alzheimer disease; scores of 2 or more indicate cognitive impairment [33] and can be completed via telephone.

#### Intervention

LSC is a virtual, social storytelling space for older adults aged 60 and older where members can share life stories and connect with other members to promote a sense of belonging, purpose, and meaning. Clubs include up to 15 members that meet once a week for 1 hour. The number of participants per group is determined based on past levels of participation where 10-15 individuals are recruited per group and 6-8 attend each session due to the nature of the population (eg, multimorbidity and acute illness). The protocol for the study will not deviate from routine LSC protocols and will be offered similarly to the usual schedule and prompts as described in the introduction except for dedicated recording sessions which will be replaced by a usual session (Table 1). Clubs are led by a nonclinician facilitator who offers prompts to trigger discussion and reminiscence. Sessions begin with greetings after which 2 prompts are offered by the facilitator. The facilitator manages the group to encourage participation by all members. To promote technology equity (colloquially referred to as “techquity”), LSC has been delivered via live video or telephone according to participant preference to promote technology inclusiveness. Participants for this study will have the option to use video or telephone based on preference. The primary endpoint for this study will be 3 months based on durations of other RT interventions [31,34]. We will additionally collect assessment data at 6 months to preliminarily determine the feasibility and efficacy of a 6-month intervention in participants who continue to participate in the intervention over a longer period. Fidelity will be assessed via periods of observation by research staff to observe if components of the intervention are met (eg, 2 prompts per session and individual participation).

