**Methods:**

A prospective, single-arm, single-center, pilot study will be conducted to compare loneliness and apathy in 50 lonely individuals without dementia at baseline who receive a virtual group reminiscence therapy intervention. The intervention will be delivered weekly over 12 weeks. Loneliness will be assessed with the UCLA Loneliness Scale and apathy will be assessed with the Apathy Evaluation Scale before and after the intervention. Feasibility will be assessed using quantitative and qualitative measures including feasibility of screening and enrollment, acceptability, and program satisfaction. Qualitative interviews will be conducted with a subset of 30 individuals to explore acceptability, barriers, and facilitators of the intervention.

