### Data Collection

Assessments will be collected via telephone at baseline, 3 months, and 6 months post RT. Participants will receive a gift card for each completed assessment. Qualitative interviews will be conducted with a subset of 30 participants to assess satisfaction with the intervention, what aspects can be improved, and explore barriers and facilitators of participation, including digital literacy. A semistructured interview guide is included in Multimedia Appendix 1. Interviews will take place at an agreed-upon location over 60 minutes and will be conducted by the primary investigator or coinvestigator. We will collect data on the following outcome measures and covariates:

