#### Feasibility Outcomes

Feasibility will be determined by screening, enrollment, and acceptability of the intervention. Acceptability of the intervention will also be assessed via program satisfaction surveys (eg, satisfaction, mood, belonging, connection with members) at 3 months and 6 months as well as qualitative interviews to explore program acceptability, barriers and facilitators of participation, and technology accessibility. Outcome measures including feasibility and health outcomes are detailed in Textbox 1 and Table 2. Benchmarks are determined by prior LSC metrics and expectations for recruitment, enrollment, and participation based on prior LSC participants. The metrics we propose are based on study-specific retention efforts (eg, preintervention counseling, relationship building with participants, and participant incentives).

Feasibility outcomes.

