**Benchmarks**
No. of individuals screened/total referred (≥70% good)No. of individuals who agree/total screened (≥70 good)No. of individuals who complete 9/12 visits/total enrolled (≥70 good)SurveyOpen-ended interviewOpen-ended interview

**Table 2 table2:** Outcome measures.

Outcome measures			Assessment		Metrics

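### Six-month feasibility and efficacy are to be judged in participants who chose to continue, a group in which poor continuation cannot show

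*Protocol article*

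**What the plan says.** The programme is fixed-length: "The intervention will be delivered weekly over 12 weeks" (Abstract, Methods), and Table 1 closes at week 12 with a special event. The Intervention section sets the main time point: "The primary endpoint for this study will be 3 months based on durations of other RT interventions". It then adds a second aim, for which 6-month data are to "preliminarily determine the feasibility and efficacy of a 6-month intervention in participants who continue to participate in the intervention over a longer period".

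Feasibility is defined under Feasibility Outcomes: "Feasibility will be determined by screening, enrollment, and acceptability of the intervention". The attendance criterion in Textbox 1 is "No. of individuals who complete 9/12 visits/total enrolled (≥70 good", so its denominator is everyone enrolled and its numerator ends at week 12. Acceptability also draws on "program satisfaction surveys (eg, satisfaction, mood, belonging, connection with members) at 3 months and 6 months", with no population or benchmark attached to the later survey.

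The assessment schedule carries no restriction to continuers: "Assessments will be collected via telephone at baseline, 3 months, and 6 months post RT" (Data Collection). Data Analysis likewise includes the 6-month time point in the repeated-measures ANOVA without naming a population. It states a sample of 50 and an expected dropout of 15%, with no time point for the dropout.

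**The concern.** Whether people carry on after a 12-week programme ends is the main thing to learn about the feasibility of a 6-month one. The Intervention section makes carrying on the condition for belonging to the group in which that feasibility is judged. A measure taken in that group cannot register people who stopped, so low uptake of the longer programme leaves no trace in it. At 12 weeks the protocol does the opposite and counts attendance against everyone enrolled.

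The same selection touches the other 6-month results. People who liked the club or felt better may be more likely to stay, so satisfaction and change scores in continuers may flatter a 6-month programme. Data Analysis says that the study is meant to supply efficacy estimates for a later randomised trial. A 6-month estimate from a self-selected group, labelled as efficacy, would be a poor input to that.

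**Working it through.** The protocol gives no derived figure on this point, so there is none to reproduce. The sample of 50 rests on pilot-study guidance, not on a power formula. The check compares two denominators.

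**Inputs from the protocol.** Enrolled: 50. Expected dropout: 15%, which leaves 50 × 0.85 = 42.5, about 42. Benchmark used at 12 weeks: 70% of enrolled, or 0.70 × 50 = 35 people. Attendance criterion: 9/12 = 75% of sessions.

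**Assumed.** The continuation rate past week 12 is not given, so a range is used. The protocol sets no 6-month benchmark; the 12-week mark of 70% serves below only as a yardstick.

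**1. Continuation.** For n continuers, the rate among continuers is n/n and the rate among enrolled is n/50.

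| Continuing (assumed) | Among continuers | Over 50 enrolled | Reaches 35 of 50? |
|---|---|---|---|
| 10 | 10/10 = 100% | 20% | no |
| 25 | 25/25 = 100% | 50% | no |
| 42 | 42/42 = 100% | 84% | yes |

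**2. Could the all-enrolled measure show a problem?** With X ~ Binomial(50, p), P(X ≥ 35) is below 0.001 for p = 0.30, 0.003 for 0.50, 0.10 for 0.60, 0.57 for 0.70 and 0.998 for 0.85. It separates poor from good continuation. The continuer-only measure is constant.

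**3. Attendance or satisfaction within continuers.** Suppose that 90% of continuers do well on some measure (assumed, and held constant). The continuer-only figure is then 90% whatever the uptake. The share of all enrolled who both continue and do well is the continuation rate × 0.90:

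- 15 of 50 continuing: 0.30 × 0.90 = 27%
- 25 of 50: 0.50 × 0.90 = 45%
- 40 of 50: 0.80 × 0.90 = 72%

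**4. Efficacy.** Assume no true mean change, and that continuing is a threshold on a normal variable correlated r with improvement. If a proportion c continues, the spurious mean improvement in continuers, in SDs of change, is r × φ(t)/c, where t is the standard normal quantile at 1 − c.

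- c = 0.50: t = 0 and φ(t)/c = 0.399/0.50 = 0.798. With r = 0.2 the bias is 0.16 SD; with r = 0.5 it is 0.40 SD.
- c = 0.85: φ(t)/c is about 0.27. With r = 0.2 the bias is 0.05 SD; with r = 0.5 it is 0.14 SD.

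Both r and c are assumptions. With r = 0 there is no bias, and with negative r it reverses.

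**The case against.** The strongest reply is that the restriction rests on one clause. Elsewhere the 6-month call, survey and ANOVA are unrestricted, so the sponsor may intend to assess everyone and to look at continuers only because a 6-month exposure can be studied only in those who receive it. This stands in part: a reader might infer that only continuers will be contacted at 6 months, or that the survey will be read only in them, and the protocol says neither. But the unrestricted sections set no 6-month feasibility measure, so the clause in the Intervention section is the only stated basis for judging it.

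Four further points stand.

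- A reader might infer that the whole 6-month result is favourable by construction. That is strictly true of continuation alone. Satisfaction, attendance and outcomes in continuers could still be poor.
- A reader might infer that the trial could not report the share of enrolled people who continue. It could: the denominator is known, and continuers must be identified in any case. The trouble is that the stated aim points to a different group.
- A reader might infer that these data will settle whether the later trial runs 3 or 6 months. The protocol says only that the study supplies preliminary data.
- The aim is additional and preliminary, and the 12-week attendance benchmark already uses everyone enrolled.

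It can also be said that a condensed article leaves such detail to the full protocol. That would answer a missing denominator. It does not answer a population that the article states.

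**Conclusion.** The point holds as a defect in the 6-month aim alone. As worded, 6-month feasibility and efficacy are judged in a self-selected group, while other sections schedule 6-month data without that limit; the sections need to be reconciled. Continuation judged in continuers is 100% whether 20%, 50% or 84% of those enrolled carry on. For satisfaction and efficacy the likely direction of bias is favourable. Under the stated model it would be about 0.05 to 0.14 SD of change at 85% continuation and 0.16 to 0.40 SD at 50%. These sizes rest on assumed continuation rates and correlations, since the protocol gives neither, and they illustrate the problem without predicting its extent. The 12-week feasibility result and the 3-month primary time point are not affected.

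**What to change.** In the Intervention section, define 6-month feasibility as the number continuing to 6 months over all enrolled participants, and show it also over those who completed the 12 weeks. If the sponsor wants a pass mark, it should be set and justified in advance; the protocol offers no basis for one beyond week 12.

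State in Data Collection and Feasibility Outcomes that the 6-month call and satisfaction survey are sought from all enrolled, whether or not they continued. This agrees with the unrestricted schedule already there. In the same edit, clarify whether the 6-month time point in Data Collection, which is worded as following the therapy, is the same one that the Intervention section describes for people still taking part.

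Label outcome and satisfaction results in continuers as descriptive, and do not present them as evidence of the efficacy of a 6-month intervention.

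The cost is a wording change, one count from attendance records, some extra 6-month calls and gift cards for people who stopped, and a 6-month figure that will probably look less favourable.

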### Data Collection

Assessments will be collected via telephone at baseline, 3 months, and 6 months post RT. Participants will receive a gift card for each completed assessment. Qualitative interviews will be conducted with a subset of 30 participants to assess satisfaction with the intervention, what aspects can be improved, and explore barriers and facilitators of participation, including digital literacy. A semistructured interview guide is included in Multimedia Appendix 1. Interviews will take place at an agreed-upon location over 60 minutes and will be conducted by the primary investigator or coinvestigator. We will collect data on the following outcome measures and covariates:

### Primary Outcome

Our primary outcomes will be loneliness and apathy. This is based on our hypothesis that targeting these cognitive decline and dementia risk factors will result in improved cognition in the longer term. Given this is a feasibility study and 3- and 6-month intervals may be too short of a time frame to see a difference in cognition and that the study will not be powered to detect differences in cognition, we propose to examine differences in loneliness and apathy, risk factors for cognitive decline, which can plausibly change in this short interval.

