**Objective:**

This study aims to explore the feasibility of a Life Story Club intervention to improve loneliness and apathy in community-dwelling older adults.

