### Study Objectives

The purpose of this study will be to explore the feasibility of a virtual group reminiscence therapy (vGRT) intervention delivered by LSC to improve loneliness and apathy in community-dwelling older adults. Rather than developing a new intervention, we propose to capitalize on an existing community-based resource to deliver a novel, virtual RT intervention directly to individuals in the community. We hypothesize that a virtual, group RT intervention will be feasible and acceptable for community-dwelling older adults.

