### Data Analysis

The primary purpose of this exploratory project is to test the feasibility of an LSC intervention and to provide estimates of the efficacy of the LSC intervention to inform a future RCT. We will enroll a total sample size of 50 participants and expect an estimated 15% dropout rate. This sample size follows guidelines for pilot studies and is appropriate for exploring feasibility [51]. Descriptive statistics will be used to report sample characteristics, feasibility markers, and measures. Statistical analyses will be conducted using Stata (version 18.5; StataCorp LLC). Repeated-measures ANOVA will be applied to test for overall differences in loneliness and apathy at baseline, 3 months, and 6 months. Secondary outcomes will be analyzed for differences in trends before and after the intervention and associations with changes in loneliness and apathy. We will test whether these measures mediate changes in loneliness and apathy from baseline using linear regression models.

We will use field notes and memos throughout the qualitative interview process to explore qualitative data. Data will be deductively analyzed using NVivo 15 software.

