The study has potential limitations. As a pilot study, the primary purpose of the proposed study is to test the feasibility of vGRT and provide preliminary efficacy data to improve loneliness and apathy. The pilot will include a single-arm and participants will not be randomized. The study will lay the groundwork for a future RCT of a LSC intervention to improve cognition in older adults. LSC engagement to date is consistent with prior work that has shown older adults can be exceptionally adherent to technological interventions with thoughtful planning and troubleshooting [52]. It is possible that technology access varies across populations and may affect the recruitment of diverse participants. We plan to collect quantitative and qualitative data regarding technology access which will inform future studies of LSC interventions. Future studies might also explore the provision of technology (eg, a tablet to allow access to videoconferencing software) to further promote access and participation. Currently, LSC is limited to 4 languages (English, Spanish, Cantonese, and Mandarin), which may exclude participants who speak other languages. In addition, the current study is restricted to individuals with and those without cognitive impairment and excludes individuals with dementia based on the AD8 assessment. The feasibility of LSC in its current format of virtual delivery, in a medium-sized group setting, with a nonclinical facilitator in individuals with advanced dementia remains an area of opportunity for future research.

In summary, this study will provide valuable data for a future RCT of a vGRT intervention to improve loneliness and apathy in community-dwelling older adults. If successful, the intervention can be widely scaled as a nonpharmacological intervention to prevent cognitive decline and promote social engagement in aging. The proposed methods to leverage community-based partnerships to establish and deliver effective interventions within communities can serve as a model for more community-engaged aging research.

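### Objective, hypothesis and benchmarks are feasibility, but loneliness and apathy are named primary and their uncontrolled single-arm change is called efficacy

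*Protocol article*

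**What the plan says.** **On purpose.** The abstract's Objective reads: "This study aims to explore the feasibility of a Life Story Club intervention to improve loneliness and apathy in community-dwelling older adults". Study Objectives gives one hypothesis: "We hypothesize that a virtual, group RT intervention will be feasible and acceptable for community-dwelling older adults". Data Analysis justifies the 50 participants as suitable for exploring feasibility, citing pilot-study guidance. Feasibility Outcomes states: "Feasibility will be determined by screening, enrollment, and acceptability of the intervention". The textbox there holds the only numeric success benchmarks: 70% or more for screening among those referred, for agreement among those screened, and for completing 9 of 12 visits among those enrolled.

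**On the primary outcomes.** The Primary Outcome section states: "Our primary outcomes will be loneliness and apathy". Its reason is a different hypothesis: "This is based on our hypothesis that targeting these cognitive decline and dementia risk factors will result in improved cognition in the longer term". Table 2 lists the two scales under primary outcomes. The feasibility measures have their own section and are nowhere called primary.

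**On use of the change scores.** Data Analysis says the project will also "provide estimates of the efficacy of the LSC intervention to inform a future RCT", and tests the two scales by repeated-measures ANOVA across baseline, 3 and 6 months. The Intervention section uses the word efficacy for a 6-month programme, assessed among people who choose to carry on. The limitations paragraph of the Discussion keeps preliminary efficacy data as a purpose, while stating that there is a single arm and no randomisation.

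**The concern.** The outcomes labelled primary do not answer the question the study says it asks. The measures that do answer it carry the benchmarks but not the label. A reader of the eventual report will look to the primary outcomes for the main result and find a before-and-after test on two scales.

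The second problem is what that test is said to deliver. Efficacy means a difference attributable to the intervention, and one uncontrolled group cannot give that. If the label stands, the pilot may be reported as evidence that the programme works, and its change score becomes available as an effect size for the trial that follows.

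**Working it through.** No stated figure is contradicted, so this is mainly a comparison of passages.

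**1. Purpose against label.**

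| Element | Refers to | Where |
|---|---|---|
| Aim | Feasibility | Abstract, Objective; Study Objectives |
| Hypothesis in the objectives | Feasible and acceptable | Study Objectives |
| Basis for 50 participants | Pilot guidance, feasibility | Data Analysis |
| Numeric benchmarks | Screening, agreement, attendance | Feasibility Outcomes textbox |
| Primary outcomes | Loneliness, apathy | Primary Outcome; Table 2 |

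Four elements point to feasibility; the primary label points elsewhere.

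**2. What a single-arm change contains.** For either scale:

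observed mean change = programme effect + time + attention + repeat assessment (+ regression to the mean, if selected on a high score)

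The design observes only the left-hand side. A concurrent control group would allow the shared terms to be subtracted; here there is nothing to subtract. Attention includes the study-specific counselling and contact described under Recruitment. Repeated-measures ANOVA tests whether the left-hand side is zero and does not separate the terms on the right.

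**3. The regression term is conditional.** The abstract's Methods describes the 50 participants as lonely. Inclusion and Exclusion Criteria lists age and language, plus exclusions for dementia, sensory loss and lack of access, with no loneliness threshold. The term therefore applies only if lonely people are in practice selected.

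**4. The 6-month statement.** Those who continue are self-selected, so the change at 6 months in that group adds selection to the terms in step 2.

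**5. What 50 participants can support.** The 95% level is my choice.

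- *Attendance benchmark* (denominator: those enrolled). 70% of 50 is 35. Wilson interval with z = 1.96: centre = (0.70 + 3.8416/100) / (1 + 3.8416/50) = 0.7384/1.0768 = 0.686; half-width = 1.96 × √(0.70 × 0.30/50 + 3.8416/10,000) / 1.0768 = 0.123. The interval is 56% to 81% (exact method: 55% to 82%).
- *Scales.* With 15% dropout, 50 × 0.85 = 42.5, so about 42 complete. The 95% interval for mean change has half-width t/√n = 2.02/√42 = 0.31 SD of the change score.

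The first interval bears on the stated question. The second gives the precision of a change, and says nothing about how much of it the programme caused.

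**The case against.** The best defence is that the article is open about its limits. It calls the project exploratory and the efficacy data preliminary, and its limitations name the single arm and the absence of randomisation. Data Analysis gives a dual purpose, feasibility plus estimates for a later trial, so the scales are not an afterthought. The Primary Outcome section explains the choice: cognition is unlikely to move in 3 to 6 months, so plausibly changeable risk factors are examined. Pilots commonly collect such scales.

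Most of this stands as mitigation. It justifies measuring loneliness and apathy, and preferring them to cognition. It does not justify ranking them above the feasibility measures. Calling an estimate preliminary describes its precision or maturity, whereas the difficulty is attribution, and the limitations paragraph never says that the change cannot be attributed to the programme.

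A reader might infer several stronger points that the text does not support:

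- *That a p-value will override the benchmarks.* No passage makes progression depend on the ANOVA, and Feasibility Outcomes says how feasibility is judged. The closing phrase in the Discussion about success is not a decision rule.
- *That the later trial will be underpowered.* The article says only that estimates will inform it, not that its target difference will be the pilot's change.
- *That the two descriptions of that trial conflict.* The Discussion speaks of "The study will lay the groundwork for a future RCT of a LSC intervention to improve cognition in older adults" and then of a "future RCT of a vGRT intervention to improve loneliness and apathy in community-dwelling older adults". The article treats loneliness and apathy as near-term risk factors and cognition as the longer-term goal, and both sentences are loose wording about another study.

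**Conclusion.** The point holds as a mismatch of labels plus a claim the design cannot support. The primary outcomes do not match the stated aim, hypothesis, sample-size basis or benchmarks, and uncontrolled change is described as efficacy in the Intervention, Data Analysis and Discussion sections.

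Its size lies in what the study may conclude: feasibility against three existing benchmarks and a description of within-person change, but no treatment effect. The bias cannot be sized from the article, which gives no SD, retest correlation or target difference, and any regression to the mean depends on a selection rule absent from the criteria. The conclusion rests on the single-arm design and the wording alone. The intervals above depend on the stated enrolment and dropout, and the conclusion does not depend on them.

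**What to change.** - Name the screening, enrolment and 9-of-12 attendance benchmarks in the Feasibility Outcomes textbox as the primary outcomes.
- Make loneliness and apathy secondary in the Primary Outcome section and Table 2, reported as mean within-person change with a 95% confidence interval.
- Replace efficacy with within-group change in the Intervention, Data Analysis and Discussion sections, including the 6-month statement about those who continue.
- State that the pilot informs the later trial through recruitment, adherence and attrition rates and through the SD and baseline-to-follow-up correlation of the scales, not through a treatment effect.

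Recruitment was planned for July 2025. If it has begun, record the change and its date before outcomes are analysed. The cost is wording and a more modest claim; no data, visits or participants change.
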